### Study endpoints

- Primary Endpoint

There will be two primary end points for determining the efficacy of the *P. vivax* national treatment guidelines:

- Treatment Failure (TF) at day 28 (see below);
- Incidence of *P. vivax* (recurrent) infection after day 28 during the 2-year follow up;

The TF is defined as the sum of early* and late** treatment failures.

- * Early Treatment Failure (ETF) (one of the following)

(i) Development of danger signs on Day 0, Day 1, Day 2 or Day 3, in the presence of parasitaemia;

(ii) Parasite density on Day 2 > Day 0 count, irrespective of axillary temperature,

(iii) Presence of parasitaemia on Day 3 with fever (axillary temperature ≥ 37.5°C),

1. Parasitaemia on Day 3 ≥ 25 % of count on Day 0.

- ** Late treatment failure (LTF)
- LTF is divided in late clinical and late parasitological failure.

Late Clinical Failure (LCF):

(i) Development of danger signs on any day after Day 3 in the presence of parasitaemia, without previously meeting any of the criteria of Early Treatment Failure;

(ii) Presence of parasitaemia and fever on any day after Day 3, without having previously meet the criteria of ETF.

Late Parasitological Failure (LPF):

Presence of parasitaemia on any day from day 7 onwards and axillary temperature <37.5 ºC, without previously meeting any of the criteria of Early Treatment Failure or Late Clinical

Failure.

*****The adequate clinical and parasitological response (ACPR)** is 1-TF. It is defined as absence of parasitaemia at the end of the follow up period (day 28), irrespective of axillary temperature without previously meeting any of the criteria of early and late treatment failure. In the adjusted estimates, patients with late asexual parasite reappearance (with or without fever) will be considered ACPR if the PCR analysis shows a new infection rather than a recrudescence.

- Secondary Endpoints

The secondary endpoints will be:

- Asexual parasite clearance time (PCT): Asexual parasite clearance time will be defined as the time (in days) from the day of randomization to 2 consecutive negative blood slides (collected at different days). The time to the event will be taken as the time to the first negative slide.
- Gametocytaemia (prevalence and density) at day 7, 14, 21, 28 after treatment;
- Hemoglobine changes between day 0 and day 14 and 28.

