## Specific objectives

1. To establish in a defined cohort of *P.vivax* patients, the short and long term efficacy of the new national treatment guideline in preventing recrudescences and relapses;
2. To characterize *P.vivax* transmission dynamics and indentify vulnerable groups among the local population (in a representative sample of the study population);
3. To set up a new tool, based on genotyping, serology and modelling able to accurately distinguish between *P.vivax* new infections and relapses.

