# MATERIALS & METHODS

## Study site and population

The study will be carried out in the 2 neighbouring communes of Tra Leng and Tra Don situated in Nam Tra My district, Quang Nam Province, Central Vietnam, where several malaria outbreaks have occurred in the past, and currently with most *P.vivax* casesin the province (11). The latter come mostly from Villages 1, 2 and 3 in Tra leng and from Village 3 in Tra Don commune. The commune health centre (CHC) of Tra leng is situated in Village 1, which is contiguous to Village 3, while Village 2 is situated at 2h walking distance through the forest on the top of a mountain. Village 4 is located even further (4h walking distance) and will be included in the study area in a second phase (March 2010) in order to increase the recruitment rate. The area is still densely forested and mountainous, a perfect site for *Anopheles dirus*, though the main vector species identified in entomological collections by the Provincial Malaria Station (PMS) is *An.minimus A,* together with other species such as *An.vagus, An.aconitus,* or *An.philippinensis* (12).

The climate is sub-humid with an average annual rainfall of about 1,200-2,000mm and two seasons: the dry season from December to April, and rainy season from May to November. Malaria transmission is perennial with 2 peaks: the first at the beginning of the rain (March-May), and the second between August and October. Annual reports from the national program show that about 40 to 45% of the malaria cases are due to *P.vivax* and all age groups are infected. The 2 communes totalled up to 400 and 300 cases, respectively in 2005 and 2006, with a total annual incidence of about 150 *P.vivax* cases/1000 populations. In 2007, the incidence dropped to 153 cases, and in 2008 only 106 cases were detected. Despite the decreasing incidence, more cases can probably be found by systematic screening.

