### Sample size calculation

Two different sample sizes were calculated: one for the estimation of *P.vivax* failure rate for chloroquine (28-day follow-up) and for Primaquine (2-year follow-up) in a cohort of *P.vivax* patients initially treated with the current radical cure regimen, and the second for the population survey on *P.vivax* prevalence (in a random sample of the study population).

- ***P.vivax population survey***

A total2,100 individuals at risk of malaria were estimated in the 4 study communes (census February 2009). According to the provincial malaria station (PMS) data on surveys carried out in April-May, the overall parasite rate was around 16% (ranging from 5 to 39% across hamlets) and the prevalence of *P.vivax* at 9%. In order to detect a minimal prevalence of 9% with 3% precision and at 5% significance level, a total of 300 individuals is needed for the survey (“CSample” command/EpiInfo6). After “finite population correction” and adding 10% security margin, a final sample size of 300 individuals would be sufficient. Since there are a total of about 370 households and in order to simplify sampling procedures, one individual in each house visited for the screening will be randomly selected to participate in the survey. This will be done by randomly choosing from the census file. The selected individual will be asked oral informed consent before starting in-depth interview.

- ***P.vivax cohort***

Between 2003 and 2007, *P. vivax* late parasitological failure to CQ was monitored in several Central Vietnam provinces and ranged from 0% to 5.7% (13). Therefore, to detect a failure rate as low as 5% with a 3% precision at 5% significance level, a minimum of 185 individuals are needed (“CSample” command/EpiInfo6). Assuming a maximum drop out rate of 10% during the first 28 days, a total of 204 cases will be necessary. For the estimation of a similar PQ failure rate after 2 years of follow-up, a total of 230 patients should be included with a maximum of 20% drop out during the 2-year follow-up.

By including 250 vivax patients in the cohort, and assuming a maximum drop out rate of 20% during the 2-year follow-up, we can expect to get a final database of 200 patients with a complete follow-up (i.e. 31 successive sampling results) for the modelling of *P.vivax* new infections/relapses.

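### The 2-year primary efficacy endpoint counts any *P. vivax* recurrence, including new infections, yet is sized and read as a primaquine failure rate of about 5%

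*Protocol*

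**What the plan says.** - **Objective (Protocol, Specific objectives).** The first objective is the short- and long-term "efficacy of the new national treatment guideline in preventing recrudescences and relapses". New infections are not part of it.
- **Endpoints (Protocol, Study endpoints).** "There will be two primary end points for determining the efficacy of the" national guideline. The first is treatment failure at day 28. The second is the incidence of *P. vivax* "recurrent) infection after day 28 during the 2-year follow up". In the adjusted day-28 estimate, late reappearances "will be considered ACPR if the PCR analysis shows a new infection rather than a recrudescence". No such rule is given for the second endpoint.
- **Sample size (Protocol, Sample size calculation).** For chloroquine, "to detect a failure rate as low as 5% with a 3% precision at 5% significance level, a minimum of 185 individuals are needed". The 2-year requirement is then introduced with the words "For the estimation of a similar PQ failure rate after 2 years of follow-up" and is set at 230 patients, allowing for 20% loss.
- **Setting (Protocol, Study site and population).** Transmission is perennial with two peaks. For 2005 and 2006 the two communes are described "with a total annual incidence of about 150" *P. vivax* cases per 1000. Counts then fall to 153 in 2007 and 106 in 2008.
- **Classification (Protocol, Blood samples processing; Data entry & Analysis).** CSP-ELISA on follow-up samples, genotyping of each recurrence and a model giving the probability that a parasitaemia is new are all planned. None is linked to the second primary endpoint.

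**The concern.** Primaquine at inclusion acts on the hypnozoites already present. It cannot prevent an infection from a mosquito bite a year later. Patients remain resident in villages with year-round transmission, so recurrence over two years is a mixture of relapse and reinfection. The Background section itself argues that efficacy cannot be judged properly while the two are indistinguishable.

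The correction is placed where it matters least, in the first 28 days, and is absent for the following 23 months. If the crude incidence is reported as efficacy of the national regimen, the result moves with local transmission as well as with the drug, and it errs in one direction: too much apparent failure.

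**Working it through.** **1. The plan's own figure.** With p = 0.05, d = 0.03 and z = 1.96, n = z²p(1−p)/d² = 202.7. The finite population correction with N = 2,100 gives 202.7/(1 + 202.7/2,100) = 184.9, that is 185. For dropout, 185 × 1.10 = 204, and 185/0.8 = 231 against the stated 230. The sizing reproduces. It shows that the 2-year result is planned as a proportion near 5%, known to within 3 points (2% to 8%).

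**2. Inputs for the background risk.**
- Follow-up after day 28: 23 months (*P.vivax* patients' treatment & cohort follow-up).
- Rate in 2005–2006: 150 per 1000 per year.
- Counts: 153 (2007) and 106 (2008). The text does not make clear whether these are *P. vivax* only or all malaria. The *P. vivax* share is given as 40–45%, so 40% and 100% are used as bounds.
- Denominator: 2,100, the census of the four initial villages. This is an assumption for the 2007 and 2008 rows, because the counts refer to two communes.

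**3. Formulas.** Background risk q = 1 − exp(−rate × 23/12), at a constant rate. Proportion with any recurrence, if true primaquine failure is 5% and independent of reinfection: 1 − 0.95(1 − q). Because community cases include relapses, each row is also run with half of the cases new. The half is an assumption; the protocol gives no share.

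| Basis | Rate per 1000/yr | q, all new | Crude result | q, half new | Crude result |
|---|---|---|---|---|---|
| 2008, 40% vivax (106 × 0.40/2,100) | 20.2 | 3.8% | 8.6% | 1.9% | 6.8% |
| 2007, 40% vivax (153 × 0.40/2,100) | 29.1 | 5.4% | 10.2% | 2.8% | 7.6% |
| 2008, all vivax (106/2,100) | 50.5 | 9.2% | 13.8% | 4.7% | 9.5% |
| 2007, all vivax (153/2,100) | 72.9 | 13.0% | 17.4% | 6.7% | 11.4% |
| 2005–2006 | 150 | 25.0% | 28.7% | 13.4% | 17.7% |

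Example, 2008 all vivax: 0.0505 × 23/12 = 0.0967; q = 1 − exp(−0.0967) = 9.2%; crude = 1 − 0.95 × 0.908 = 13.8%.

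**4. Break-even.** Reinfection equals 5% over 23 months at −ln(0.95)/(23/12) = 0.0268, about 27 per 1000 per year.

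**5. In patients.** Among 200 completers, 5% is 10 primaquine failures. Background infections would number about 8 (3.8%) to 50 (25.0%), or about 4 to 27 if half of the cases are new.

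**6. Reading.** With all cases new, every crude result lies above the 8% upper edge of the planned precision. With half new, the two 40%-vivax rows (6.8% and 7.6%) stay inside it and the other three do not.

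**The case against.** **The protocol knows the problem.** Separating relapse from new infection is a stated purpose of the study, the Summary lists efficacy and the incidence of new infections as two quantities, and the data to separate them will be collected. How classified recurrences enter an estimate is often left to a statistical analysis plan, which is not at hand. This stands in part: what is missing is a link, not data. But the endpoint definition and its role as a measure of efficacy are fixed in the protocol, and there the day-28 endpoint has an adjustment and the 2-year one has none.

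**Failure is not defined after day 28.** A reader might infer that the protocol classes every later recurrence as treatment failure. It does not: Study endpoints defines treatment failure for day 28 only. The failure reading arises when the endpoint is joined to the sample size wording.

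**The largest figures are the least applicable.** A reader might infer that reinfection will swamp primaquine failure. The 25% rests on a rate from before the 2007 change of regimen and before the fall in cases, and counts all community cases as new. At the lowest 2008 reading with half new, reinfection adds under 2 points (6.8% against 5%). In the other direction, monthly slides will detect infections that routine reporting misses.

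**The observed endpoint has merit.** Crude recurrence needs no unproven tool and bounds detected relapse from above. This stands, and is a reason to keep it beside an adjusted figure rather than replace it.

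**Conclusion.** The point holds as a mismatch between objective, endpoint and sample size. The 2-year endpoint measures any recurrence; the objective and the planned failure rate concern relapse and recrudescence. Used as written, it gives an estimate of primaquine failure that is biased upwards.

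The background risk is about 4–9% at 2008 levels and up to 25% at the 2005–2006 rate, or about 2–13% across the whole range if half of the cases are new. Matching or exceeding 5% is supported over much of that range, but not at its lowest end. The figures assume a constant rate, independence of relapse and reinfection, the 2,100 denominator and the stated vivax shares.

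A reader might also conclude that the first objective cannot be answered. The documents do not support that: genotyping, serology and the model could answer it once they are tied to the endpoint.

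**What to change.** In Study endpoints, state the 2-year endpoint as a pair, as is already done at day 28:

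- **Crude:** incidence of any *P. vivax* recurrence after day 28, labelled as recurrence and not as primaquine failure.
- **Adjusted:** relapse or recrudescence of the inclusion infection, using the planned genotype, CSP and model classification. Base it on the first recurrence, or censor at the first recurrence or likely new infection. Recurrences are treated with chloroquine alone, so relapses of a later infection could otherwise be counted against the inclusion course. Restricting to first recurrences is not enough without the classification, since a first recurrence can itself be new. Carry the classification uncertainty into the interval, because the model is fitted to these same patients.

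In Sample size calculation, tie the primaquine failure rate to the adjusted estimate.

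The cost is a change of wording and some analysis; the assays are already planned. The adjusted figure will depend on a tool still under development and will have a wider interval, which is why the crude figure stays beside it.

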# BACKGROUND

According to the national control program (NMCP), half of the malaria morbidity and about 90% of its mortality occurs in the 16 forested provinces situated in Central Vietnam (1, 2). In these areas, *Plasmodium vivax* represents about half of all malaria cases (3, 4), and the local populations bear a heavy morbidity burden due to the activation (relapses) of dormant liver forms (hypnozoites) weeks or months after the primary infection. Hypnozoites can be treated with a 2-week course of primaquine as recommended by WHO (5). However, treatment adherence is usually low and self-treatment with inappropriate drugs or inadequate dosage is common as symptoms are often mild. Therefore, Vietnam has recently (2007) doubled the daily dose of Primaquine (from 0.25 to 0.5mg/kg) in its 10-day protocol (6). However, the efficacy of this new regimen in preventing short- and long-term relapses has not yet been formally evaluated. Moreover, the epidemiology of *P.vivax* is poorly documented because the currently available techniques cannot discriminate between relapses/recrudescences and new infections. Therefore, the incidence of new infections and related risk factors cannot be estimated, the current treatment efficacy and the impact of control activities cannot be accurately evaluated and new interventions cannot be tested. This results in a *statu quo* as control strategies cannot be adapted to the local epidemiology, and consequently maintains the vulnerability of local populations, mainly ethnic minorities with poor health and socio-economic status. We propose to set up a new tool that will assist the NMCP in understanding the transmission dynamics of *P.vivax*, in monitoring the treatment efficacy, and in designing and evaluating targeted strategies to control *P.vivax* malaria. This method will combine molecular, serological and epidemiological markers that will be incorporated in a mathematical model to estimate the probability for a given vivax episode to be a new infection. Similar models have already been developed for *P. falciparum* (7) and will be adapted for *P. vivax*. Currently, the best molecular markers for *P.vivax* genotyping are micro-satellites (MS), which are highly polymorphic tandem repeats. However, genotyping alone is not sufficient since a true relapse could have a different genetic pattern from the primary infection (8), due to different parasite clones present in the liver. Thus, recent exposure to an infective mosquito bite needs also to be checked by measuring antibody titres against *P. vivax* circumsporozoite protein (CSP), short-lived (1 month) and specific against sporozoites. This can be done with an existing CSP Enzyme Linked Immunosorbent Assay (ELISA) (9-10). MS markers and CSP-ELISA are currently under development at ITM, Antwerp.

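### The PCR-adjusted day-28 response has no class for relapse, so a genetically different relapse can be scored as success in the adjusted estimate

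*Protocol*

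**What the plan says.** Study endpoints introduces the endpoints with "There will be two primary end points for determining the efficacy of the" national P. vivax treatment guidelines. The first is treatment failure (TF) at day 28: "The TF is defined as the sum of early* and late treatment failures". No genotyping enters that definition. The second is the incidence of recurrent P. vivax infection after day 28, over the two-year follow-up. ACPR is one minus TF. For the adjusted estimates only, a patient with late reappearance of asexual parasites "will be considered ACPR if the PCR analysis shows a new infection rather than a recrudescence".

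Four other places bear on that rule:

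- **Background:** "genotyping alone is not sufficient since a true relapse could have a different genetic pattern from the primary infection". It goes on to say that "recent exposure to an infective mosquito bite needs also to be checked by measuring antibody titres against" the P. vivax circumsporozoite protein (CSP).
- **Specific objectives, first item:** "the short and long term efficacy of the new national treatment guideline in preventing recrudescences and relapses".
- **Sample size calculation:** the target is described as the "failure rate for chloroquine (28-day follow-up) and for Primaquine (2-year follow-up"), which reads the 28-day result as a chloroquine result.
- **Blood samples processing, and Data entry & Analysis:** CSP-ELISA is planned on the 28-day and monthly samples to help identify new infections. A model is to give the probability that any P. vivax parasitaemia is a new infection. The adjusted ACPR rule refers to neither.

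**The concern.** The rule sorts late recurrences into two classes by one test. The Protocol elsewhere recognises three origins (new infection, recrudescence, relapse) and says that this test alone cannot tell two of them apart. A relapse from a different liver-stage clone would show a genotype that differs from day 0. Under a new-infection-or-recrudescence choice it would naturally be read as a new infection, and the patient would become a success. Under the first specific objective the same event is a failure of the regimen.

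For relapses the error runs one way, towards higher adjusted efficacy. This is not a detail that can be left to an analysis plan: the rule is fixed in the endpoint section and conflicts with the premise on which the study is built.

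**Working it through.** **Inputs.** Sample size calculation gives a planning failure rate of 5%, precision of 3 points, 5% significance level, a population of 2,100 and n = 185. It cites late parasitological failure between 0% and 5.7%. No section gives the share of late recurrences that are genetically different relapses. Call that share h and let it run from 0 to 1.

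**Step 1: the plan's own figure.** n0 = z² p(1 − p)/d² = 1.96² × 0.05 × 0.95 / 0.03² = 202.7. With finite population correction, 202.7 / (1 + 202.7/2,100) = 184.9, so 185. The figure reproduces; it is not in dispute and only sets the scale.

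**Step 2: size of the possible overstatement.** Let L be the late recurrence rate. If relapse counts as failure, the rule moves L × h of patients from failure to success. Overstatement of adjusted ACPR, in percentage points:

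| L | h = 0 | h = 0.25 | h = 0.50 | h = 0.75 | h = 1 |
|---|---|---|---|---|---|
| 1% | 0 | 0.25 | 0.50 | 0.75 | 1.0 |
| 3% | 0 | 0.75 | 1.50 | 2.25 | 3.0 |
| 5% | 0 | 1.25 | 2.50 | 3.75 | 5.0 |
| 5.7% | 0 | 1.43 | 2.85 | 4.28 | 5.7 |

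At 5% this is 0 to about 9 of 185 patients (185 × 0.05 = 9.25). It exceeds the planned 3-point precision only if h is above 3/5 = 0.6.

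**Step 3: the opposite error.** A true new infection can match the day-0 genotype by chance and then stays a failure. Let r be the share of late recurrences that are new infections and m the chance-match probability. True failure is L(1 − r). PCR-adjusted failure is L[(1 − h − r) + r m]. The net overstatement of ACPR is the difference, L(h − r m). Illustrations at L = 5% and r = 0.5 (h, r and m are all assumed):

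- h = 0, m = 0.1: −0.25 points
- h = 0.05, m = 0.1: 0 points
- h = 0.2, m = 0.1: +0.75 points
- h = 0.1, m = 0.3: −0.25 points

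The net sign therefore depends on unknown quantities, and PCR-only failure is not a lower bound on true failure.

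**Step 4: is the missing evidence available?** Table 2 schedules filter papers for ELISA and PCR on D0, D2, D3, D7, D14, D21, D28 and at unscheduled visits. The Day 0 procedures plan ELISA on all 28-day samples and genotyping of late failures. The second marker that the Background asks for will exist; the rule does not use it.

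**The case against.** Three objections carry weight.

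- **The primary endpoint is not touched.** A reader might infer that the rule biases a primary endpoint. The text does not support that. TF as listed counts every late recurrence as failure, and PCR enters only through the later sentence on adjusted estimates. Recurrences after day 28 go to the second primary endpoint, with no PCR exclusion. This objection stands in full. The Protocol does not, however, say which day-28 figure leads the report.
- **The 28-day window may be meant for chloroquine only.** Sample size calculation says so. On that reading, leaving a relapse out of a blood-stage failure rate is defensible. But Study endpoints and Specific objectives frame efficacy as that of the whole guideline, including relapse prevention. The sections disagree, and even on the narrower reading a relapse labelled as a new infection is misclassified.
- **The size is unknown.** A reader might infer that most relapses become successes, or that adjusted failure is understated several-fold. Neither follows. The Background says only that a relapse could differ genetically. A title in the reference list says that relapses are usually heterologous, but gives no share for recurrences within 28 days of supervised primaquine. Relapses are described as coming weeks or months later, so few may fall in the window, and h may be zero.

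It can also be said that the planned serology and model already solve the classification. They would, if the rule referred to them.

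**Conclusion.** The point holds for the adjusted day-28 estimate only. The rule allows a genetically different relapse to be scored as an adequate response, against the Protocol's own statement about genotyping and its own efficacy objective. Adjusted ACPR can be overstated; the documents do not show that it will be. The range is 0 to 5 points at the 5% planning rate and 0 to 5.7 points at the top of the cited range. It rests on three assumptions: relapse counts as failure, a different genotype is read as a new infection (the match criterion is not stated), and chance matches are set aside. It should be corrected, but it does not invalidate either primary endpoint.

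**What to change.** Revise the adjusted-ACPR sentence in Study endpoints as follows.

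1. State that unadjusted TF is the main day-28 estimate and that the adjusted figure is supplementary.
2. Add a relapse/indeterminate class. Score a late recurrence as ACPR only when a differing genotype is supported by CSP serology or by the model probability of new infection described in Data entry & Analysis. Otherwise keep it as failure. Fix the criterion before the late recurrences are classified. Read serology against the patient's earlier samples: the Background gives the antibody a life of about one month, so a single positive result may be left over from the primary infection. A rigid titre-rise threshold is not advisable while the assay is still being standardised.
3. Report the PCR-only figure as a sensitivity analysis, not as a bound.
4. Reconcile Sample size calculation (28 days as chloroquine failure) with Specific objectives and Study endpoints (efficacy of the whole guideline), and say which one the adjusted estimate targets.

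The cost is wording and analysis; the samples and assays are already planned. Adjusted efficacy may look slightly less favourable, and some true new infections will remain counted as failures.
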